### **3 STUDY POPULATION**

#### **3.1 NUMBER OF PARTICIPANTS**

Approximately 170 participants from each of 60-80 general practices in the most deprived quintile of the population Scotland (from a total of 200 in that quintile) as measured by the quintiles of the Scottish Index of Multiple Deprivation (SIMD) 2012 - version 2.

#### **3.2 INCLUSION CRITERIA**

1. Participant is willing and able to give informed consent for participation in the study
2. Male or female aged 50 years to 75 years
3. Current or Ex-smoker with at least 20 year pack history
4. or Less than 20 year pack history but with family history of lung cancer in a 1st degree relative (mother, father, sister, brother, child)
5. ECOG Status: 0, 1 and 2 (Eastern Co-operative Oncology Group)

| Grade | ECOG                                                                                                                                               |
|--------------|-----------------------------------------------------------------------------------------------------------------------------------------------------------|
| 0            | Fully active, able to carry on all pre-disease performance without restriction                                                                            |
| 1            | Restricted in physically strenuous activity but ambulatory and able to carry out work of a light or sedentary nature, e.g., light house work, office work |
| 2            | Ambulatory and capable of all self-care but unable to carry out any work activities. Up and about more than 50% of waking hours                           |

6. Geographical postal sectors of:

| NHS Geographical Area              | Eligible Postcodes                                                                                                                                                     |
|------------------------------------|------------------------------------------------------------------------------------------------------------------------------------------------------------------------|
| Tayside                     | DD1 - DD11 (except DD6), PH1–PH3 , PH6-PH8, PH10, PH11, PH13, PH15 & PH16                                                                                              |
| Greater Glasgow & Clyde | G1-G5, G11 –G15, G20-G22, G31-34, G40 –G46,

G51- G53, G60-G62 &G64, G66 & G69, G72 & G73,

G76-G78, G81-G83

PA1–PA8 (except PA6), PA11-PA16 & PA19 |

### 3.3 EXCLUSION CRITERIA

1. History of any cancer other than non-melanomatous skin cancer, cervical cancer in situ.
2. Symptoms suggestive of lung cancer within past 6 months (haemoptysis, unintentional weight loss (at least 5% in preceding 6 months).
3. Patients for whom the GP considers invitation to the study would cause undue distress.
4. Patients with other terminal disease.
5. Patients on prolonged / continuous use (> 3months) of cytotoxic/ immuno-suppressant drugs eg: Methotrexate, Cyclophosphamide, Azathioprine, Rapamycin, Mycophenolate, Rituximab and anti-immunophilins such as Ciclosporin, Tacrolimus. Monotherapy using glucocorticoids/ steroids eg prednisolone is NOT an exclusion criteria.

## **4 PARTICIPANT SELECTION AND ENROLMENT**

### **4.1 IDENTIFYING PARTICIPANTS**

Potentially eligible individuals will be identified from GP medical records by an electronic medical record search undertaken by the Scottish Primary Care Research Network. Potential participants will be recruited via their General Practitioner (through SPCRN) using a range of methods including:

- a.** postal invitation letter including a summary of the study Participant Information Sheet and a full PIS or Participant Information Brochure for those interested;  
  
and, where necessary or appropriate:
- b.** invitation letter including a summary of the study Participant Information Sheet on collection of repeat prescription;
- c.** invitation during consultation with GP / Practice Nurse / Health Care Assistant at the practice;
- d.** invitation to those eligible on registered research volunteer databases
- e.** poster present in the GP's waiting room;
- f.** other recruitment strategies may be employed including; Media campaign involving: local and national newspapers; BBC Scotland; local radio, Celebrity endorsement
- g.** Publicity campaign using posters/leaflets etc....including:  
  
Football/Bingo halls/ Bowling  
  
Smoking Cessation Clinics  
  
Hospital main entrances/ hospital clinics  
  
Shopping Centres/Supermarkets/Pubs/etc.

Benefits offices/Post offices etc.

Sheltered Housing /Housing Associations

Community and charitable outreach programs

Mobile screening clinic

Pharmacist approach through practices.

The study invitation letter will include a slip for participants to either express interest in finding out more about the study, and provide their contact details or to request no further contacts about the study. Those returning an expression of interest will be telephoned, more than 24 hours after anticipated receipt of the Participant Information Sheet/PIB, by a member of the research team.

Additionally, the participant is given the opportunity to call or email the study team. The call (instigated by participant or study team) will allow a discussion of the study, to answer any questions the potential participant may have, do a preliminary assessment of eligibility and if they agree, to make an appointment for a recruitment visit (hereafter referred to as the eligibility assessment phone contact). An appointment letter/email will be sent out to confirm appointment.

A reminder call/email or text, whichever is preferable to the participant, will be carried out 2 days prior to the screening appointment. A reminder process decreases non-attendance.

Non-responders to the postal invite will be approached again, and for the last time, no longer than 2 months after the initial contact.

Where the recruitment rate falls short of the required number at each practice (170 per practice), practices will attach study invitation letters to repeat prescriptions of those aged between 50 years and 75. Those returning an expression of interest will be sent a full PIS/PIB and dealt with as above.

We will offer participating practices the option of using the Trial Torrent software package to identify potentially eligible patients who do not respond to the postal trial invite so that they can be approached during routine primary care consultations and given the study invite letter and Participant Information Sheet. Where potential participants express interest during the consultation, the software will notify the research team of that expression of interest. A member of the research team will undertake the eligibility assessment phone contact for those expressing interest in the consultation or by returning the expression of interest form at a later date. The recommended order (findings from focus groups) is;

- obtain consent
- take bloods from all consented participants (in the unlikely event; a blood sample is unobtainable or the blood sample blood sample from a participant in the test group is lost during transportation the participant will be contacted to arrange a subsequent sample.)
- complete survey questionnaire
- randomise to treatment arm

After randomisation group allocation is known all participants will be asked if they continue to be happy for their bloods to be used for the Early CDT- Lung Test (lung cancer test group) and for future cancer related research for those who agreed by initialling the relevant box on the consent form.

For participants randomised to the intervention arm the EarlyCDT-Lung test will be performed and patients followed up according to their result.

At Visit 1 participants are advised that those with a positive EarlyCDT-Lung test result will be invited to a follow-up visit to interpret the test results and explain the progress on study thereafter. Those with a negative EarlyCDT-Lung test result will be

written to, explaining the test results and will be offered a follow-up visit or a telephone call if they wish. They will be advised of symptoms to watch for including persistent cough, coughing up blood, shortness of breath, weight loss or loss of appetite. They will be counselled to carry on having tests for other types of cancer if they are offered (e.g. bowel cancer test, mammograms, cervical smears).

Those in the control arm will be written to and thanked for their contribution to the study and advised and counselled identically to those with a negative test result.

All participants who agreed to donate blood for future will be advised that it will be used in cancer related research.

A patient specific section of the study website ([www.eclsstudy.org](http://www.eclsstudy.org)) containing Participant Information Sheets and research staff contact details will be available for participants to view.

## **4.2 CONSENTING PARTICIPANTS**

All individuals taking informed consent will have received training in Good Clinical Practice (GCP). It will be explained to patients that they are under no obligation to enter the trial and that they can withdraw at any time during the trial, without having to give a reason. A copy of the signed Informed Consent Form (ICF) will be given /or posted out to the study participant. A copy of the signed consent form will be given or sent to the GP with a letter outlining the study and patient pathway. The letter will notify the GP of their patients' group allocation, relevant Early CDT-Lung test result, and any notable findings found at the screening visit, namely, the request to give up smoking or relevant clinical information that requiring further clinical judgement. The original copy of the ICF is to be retained at the study site (ISF or TMF, as appropriate.). If any notable findings are found at the screening visit an anonymised copy of the GP letter will be filed in the participant's study file. If new safety information results in significant changes to the study risk–benefit assessment, the

Protocol, Participant Information Sheet and/or consent form will be reviewed, updated and amended as necessary. All participants will be informed of the new information, given a copy of the revised consent form and asked to re-consent if they choose to continue in the study.

#### **4.3 SCREENING FOR ELIGIBILITY**

SPCRN staff will visit practices to undertake searches of the GP computerised records. The resulting list of potentially eligible participants will be checked by a GP at the practice to ensure that those for whom study participation would cause undue distress and those with a terminal disease are not sent study invitations. Telephone screening of potentially eligible participants who have returned an expression of interest will be undertaken by a member of the research team at the eligibility assessment phone contact. This will include assessment of age, smoking history, family history of lung cancer, previous cancer, ECOG status and eligible postcode.

#### **4.4 INELIGIBLE AND NON-RECRUITED PARTICIPANTS**

The reason(s) for ineligibility will be explained to the patients and any questions they have will be answered. They will be thanked for their interest in the trial and any relevant clinical information will be communicated to their GP where the patient has given consent.

#### **4.5 RANDOMISATION**

Participants will be allocated to intervention or comparison group during the recruitment visit (Visit 1) using a web-based randomisation system; TRuST, provided by Tayside Clinical Trials Unit (TCTU). Set-up of the randomisation system will be by TCTU staff under the supervision of a TCTU statistician. Randomisation will be stratified by site and minimised by age, sex and smoking history

## **4.6 ADMINISTRATION OF THE TEST**

Individuals at higher risk will be identified from GP medical records or community based recruitment as described above. Consenting individuals will be randomised to either receive an EarlyCDT-Lung test or standard care.

## **4.7 MANAGEMENT OF THE VISITS**

Based on the test's 93% specificity and 41% sensitivity we anticipate that 400-450 participants in the intervention arm will have a positive test result. These will be offered a chest X-ray. Those with a negative or indeterminate X-ray will be referred for a CT scan. If the initial CT is negative then subsequent CTs will be offered 6 monthly for 24 months. Participants will receive appointments via mail/email (as preferred). Participants will be called 2-4 days before each CT-scan appointment. By calling, this allows the participant to ask any questions, check health status, arrange transport (if required) and increase participant retention. Individuals with monitorable abnormalities as classified by the radiology/respiratory physician's study panel on baseline CT scan or subsequent CT will be followed up over the study period or referred for NHS clinical care as appropriate. All individuals entering the study will be flagged and followed-up via the Scottish Cancer Registry. Participants who develop lung cancer will be individually followed-up via their medical records to assess both time to diagnosis and stage of disease at diagnosis. If no histological stage is available, stage will be assessed by a panel of three respiratory physicians blind to allocation status of the study subjects from chest X-rays or CT, or, if no imaging is available, medical assessment of stage will be carried out.

Prior to sending CT scan appointments participant deaths will be checked using the SMR to ensure sensitivity is maintained. All participants in the EarlyCDT- Positive test groups known to have died will be removed from the CT scan appointment schedule register. If patients (EarlyCDT-Positive test) fail to attend for any imaging

assessment during the study, they will receive two reminders (one letter, one phone call). On the third non-attendance, a letter will be sent to the participant's GP to inform them of non-attendance. An appointment window of  $\pm 4$  weeks will be initiated for each scheduled CT scan.

Participants will receive results letters in relation to their initial CXR and CT scan and subsequent CT scans. Any clinical intervention/treatment will be arranged by the study team.

#### **4.8 WITHDRAWAL AND STUDY TERMINATION PROCEDURES**

No circumstances are anticipated for the withdrawal of patients from the trial initiated by the clinical team or trial investigators. Patients may choose to withdraw from the trial at any time, without giving a reason, and without compromising their future treatment.

If the study should be terminated early, for whatever reason, all participants with a positive Early CDT-Lung test will continue to be seen by the PI (lung specialist) and will continue to undergo any clinically relevant investigations and reviews and will be treated (if required) according to current clinical practice.

### **5 STUDY AND SAFETY ASSESSMENTS STUDY ASSESSMENTS**

The main study assessment is the test result.

Other assessments include;

- diagnosis
- costs associated with intervention including any follow up/confirmatory tests and subsequent treatment
- costs associated with routine clinical management of patients

- health utility data
- mortality (various)
- measures of psychological outcomes and health behaviour
- other clinical outcomes uptake of subsequent investigations

## **5.1 SAFETY ASSESSMENTS**

As the study does not employ an Investigational Medicinal Product, Adverse Events (AE) or Serious Adverse Events (SAE) will be recorded but not reported in the Annual Report. A number of factors affecting the trial population suggest that we would expect to observe a larger than normal incidence of episodes of ill-health due to both the age and co-morbidities of the study population. All known disease progressions and co-morbidities will be regarded as outcomes including complications arising from investigations which result in a hospital stay which will be captured in outcome 6 and all medical treatment or interventions will be predicated upon normal clinical care and not related to the study protocol. All CXR and CT scan incidental findings (incidentaloma) will be recorded in the CRF as an incidental finding and a specialist referral will be made as directed in a study SOP within the Study Operations Manual. AEs (as defined) will be recorded as soon as they are known either from the study subjects, PI patient review audits or via SMR or record review.

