|          |                                                                                                                                                                                  | (all participants in the EarlyCDT-positive group will be approached with the recruitment aim of 300 from this group collected at 1,3,6,12,18 and 24 months. The EarlyCDT-negative and control groups will be recruited at the same rate as the EarlyCDT-positive group with the recruitment aim of 300 from each group collected at 1,3,6 and 12 months). |
| 6 | to assess the effectiveness of EarlyCDT-Lung test on other clinical outcomes such as CVD, COPD, other cancers, hospital stays and outcomes identified through SMR linkage, etc.; | Incidence of other clinical outcomes such as CVD, COPD, other cancers, hospital stays, identified through SMR linkage, measured at 24 months, 5 and 10 years in the intervention arm and in the control arm; assessment of significance of differences;                                                                                                   |
| 7 | to assess uptake of subsequent investigations such as CXR, CT, bronchoscopy, etc.                                                                                                | numbers in all groups (EarlyCDT-Lung test-positive, EarlyCDT-Lung test-negative, control) undertaking subsequent investigations such as CXR, CT, bronchoscopy, etc.                                                                                                                                                                                       |

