6) incidence at baseline, 24 months, and after 5 years and 10 years, in other clinical measures such as CVD, COPD, other cancers, hospital stays, and outcomes identified through SMR linkage, etc. in the intervention arm and in the control arm; assessment of significance of differences;

7) numbers in all groups (EarlyCDT-Lung test-positive, EarlyCDT-Lung test-negative, control) undertaking subsequent investigations such as CXR, CT, bronchoscopy, etc.

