| CT Scan*                                                                                                                | X                       | X                                                                                                                   | X                    | X                                                                                                                                                                            | X         |
| *Scheduled every 6 months, if participant enters NHS clinical care pathway, subsequent study CTscans will be cancelled. |                         | Research team member will call 2-4 days before each scheduled CT scan to check health status and attendance. |                      |                                                                                                                                                                              |           |

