## **7.2 PROPOSED ANALYSES**

Characteristics of participants will be compared informally between treatment arms at baseline. The main analysis of the primary outcome will be intention-to-treat. Cox proportional hazards models will be used to estimate the hazard ratio of the rate of late stage lung cancer in the intervention arm compared to the control arm.

Participants who are lost to follow up will be censored. The models will adjust for age, gender smoking history and practice. If appropriate, random cluster effects will be included rather than fixed effects for practices. A similar methodology will be used for the secondary outcomes of comparisons of mortality rates (secondary outcomes 3a and 3b). A subsequent analysis will compare the outcomes of those with EarlyCDT positive in comparison to those in the intervention group with EarlyCDT negative (primary contrast for this analysis) and those in the control group (secondary analysis 1). Comparisons of proportions (secondary analyses 1 and 4) will be carried out using chi square tests. Fishers exact test will be used if the numbers of events are small.

The analyses of the questionnaire responses (secondary analysis 5) will be carried out using the appropriate 2 sample t tests and regression methods at baseline. Non parametric tests will be used if there is evidence of non-normal scores. Multilevel models will be used to analyse the repeated scores during follow up.

Poisson regression models, adjusting for follow up time if necessary, will be used to investigate the other clinical measures (secondary outcomes 6 and 7).

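### Outcome 6 judges CVD, COPD and other cancers by between-arm incidence, although protocol chest imaging with referral reaches only intervention-arm test-positives, so detection can be read as effect

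*Protocol*

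**What the plan says.** - **Outcome.** The summary table of objectives and outcomes defines outcome 6 as "Incidence of other clinical outcomes such as CVD, COPD, other cancers, hospital stays, identified through SMR linkage, measured at 24 months", and again at 5 and 10 years. Section 1.5.2 makes it a contrast "in the intervention arm and in the control arm; assessment of significance of differences". The matching research question in section 1.2 is whether the test improves these outcomes.
- **Model.** Section 7.2 assigns Poisson regression to outcomes 6 and 7. Follow-up time is the only adjustment it names.
- **Imaging.** Section 4.7 expects 400-450 positive tests in the intervention arm and offers those participants a chest X-ray and then CT. Table 1 in section 2.4 lists CT at 0, 6, 12, 18 and 24 months, with the note "Scheduled every 6 months, if participant enters NHS clinical care pathway, subsequent study CTscans will be cancelled". Section 8.7.3 says that people with a negative test get no X-rays or scans. The Comparator paragraph of the Summary leaves controls to be investigated when symptoms appear.
- **Incidental findings.** Section 5.1 states that they are "recorded in the CRF as an incidental finding and a specialist referral will be made as directed in a study SOP". The flowchart in section 2.2 sends results judged clinically significant to routine NHS follow-up.
- **Morbidity as outcome.** Section 5.1 also says "All known disease progressions and co-morbidities will be regarded as outcomes including complications arising from investigations". The clause that follows places complications leading to a hospital stay in outcome 6.

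**The concern.** The linkage is the same in both arms, but the process that produces diagnoses is not. A chest CT series in long-term smokers images the heart, great vessels, lungs and neighbouring organs, which are sites of the diseases outcome 6 names. A scan finding that is referred, confirmed and coded becomes an incident case in the intervention arm. The same disease in a control, or in a test-negative participant, stays unrecorded until it presents.

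Extra detection moves the incidence ratio in the direction opposite to benefit. On a question framed as improvement, a ratio above 1 would be read as harm, and a true reduction could be cancelled. Nothing in the protocol separates scan-prompted from clinically presenting diagnoses for outcome 6. For lung-cancer stage, section 4.7 does guard part of the assessment: where no histological stage exists, a panel blind to allocation assigns it. Outcome 6 has no comparable safeguard.

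**Working it through.** **Inputs from the protocol**
- 5,000 per arm (section 7.1).
- 400-450 intervention-arm positives (section 4.7). This can be checked from 41% sensitivity and 93% specificity: 5,000 × (0.41 × prevalence + 0.07 × (1 − prevalence)) gives 384, 401 and 435 at prevalences of 2%, 3% and 5%. The stated range therefore reproduces for a prevalence of about 3% or more.
- Share of the arm eligible for imaging: 400/5,000 = 8% to 450/5,000 = 9%.

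**Inputs the protocol does not give, so assumed**
- Background two-year incidence p of the outcome: 5% or 10%.
- Yield y, the share of scanned participants who gain one extra coded diagnosis of that outcome because of imaging: 2% to 20%.
- All positives are scanned, and the test has no true effect.

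**Formulas**
- Extra cases = (400 to 450) × y × (1 − p).
- Intervention-arm incidence q = p + extra/5,000, and risk ratio = q/p.
- Chance of a significant result in the harmful direction ≈ Φ((q − p)/SE − 1.96), where SE = √(2 × m × (1 − m)/5,000) and m is the mean of p and q. The nominal value is 2.5%.

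**One case in full** (p = 5%, y = 10%, 400 scanned)
- Extra = 400 × 0.10 × 0.95 = 38.
- q = 0.05 + 38/5,000 = 0.0576, so the risk ratio is 0.0576/0.05 = 1.15.
- m = 0.0538 and SE = 0.00451, so z = 0.0076/0.00451 = 1.68.
- Chance = Φ(1.68 − 1.96) = Φ(−0.28), about 39%.

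**Results** (ranges run from 400 to 450 scanned)

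| Background p | Yield y | Extra cases | Risk ratio | Chance of significant apparent harm |
|---|---|---|---|---|
| 5% | 2% | 8-9 | 1.03 | 5-6% |
| 5% | 5% | 19-21 | 1.08-1.09 | 13-16% |
| 5% | 10% | 38-43 | 1.15-1.17 | 39-47% |
| 5% | 20% | 76-86 | 1.30-1.34 | 90-95% |
| 10% | 5% | 18-20 | 1.04 | 9-10% |
| 10% | 10% | 36-41 | 1.07-1.08 | 22-26% |
| 10% | 20% | 72-81 | 1.14-1.16 | 64-74% |

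**Masking.** At p = 5% the control arm has 0.05 × 5,000 = 250 cases. At a 10% yield, 38-43 extra cases would roughly cancel a true reduction of 38/250 = 15% to 43/250 = 17%.

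**Timing.** The last CT is at month 24 with a window of ±4 weeks (sections 2.4 and 4.7), and section 10.4 sends incidental findings for further investigation after the last scan. Scan-prompted diagnoses can therefore fall on either side of the 24-month cut.

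**The case against.** **Real consequence, not error.** Under intention-to-treat, extra diagnoses and the care that follows are genuine effects of the screening strategy, and the trial sets out to measure morbidity, harms and benefits. This stands. It is why the comparison should be kept; the fault lies in reading it as disease caused or prevented.

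**The chain to coded events is not documented.** Outcome 6 comes from SMR linkage, whereas incidental findings go in the CRF. A reader might take "All known disease progressions and co-morbidities will be regarded as outcomes including complications arising from investigations" to mean that every scan finding counts in outcome 6. The text does not support that: the explicit link to outcome 6 is for complications leading to a hospital stay. A reader might also infer that every finding is referred. Section 5.1 makes referral subject to an SOP, and section 2.2 limits NHS follow-up to results judged clinically significant. Coding of such diagnoses is plausible but not shown, so a rise in incidence is the expected direction and not an established fact.

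**A clean break at 24 months.** It is tempting to say that the distortion belongs to the first 24 months only. Work-up of the month-24 scan runs later, and controls may catch up by 5 and 10 years.

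**The size is assumed.** Non-attendance, findings spread over several outcomes, and participants who already have CVD or COPD (not excluded by section 3.3) would all lower the yield for any one outcome. Section 5.1 expects more ill-health than normal, which points to a higher background and a smaller ratio. At a 2% yield the distortion is slight. All of this stands, and it limits the size rather than removing the mechanism.

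**SAP content.** Code lists and tabulations commonly sit there. The outcome, the arm contrast, the significance test and the model are fixed in this protocol, though, and an SAP written to it would inherit them. The absence of covariates is not itself the fault, because no covariate would remove a difference in detection.

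**Existing alternatives.** Mortality (outcomes 3a and 3b), hospital stays (in outcome 6) and the count of investigations (outcome 7) help. None of them gives a condition-specific, less detection-sensitive comparison for CVD or COPD.

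**Conclusion.** The concern holds as a risk of biased interpretation on one secondary outcome. The protocol tests between-arm incidence of CVD, COPD and other cancers to judge whether the test improves them, while protocol imaging with SOP-directed referral reaches 8-9% of one arm and nobody in the other. Scan-prompted diagnoses that reach the linked records can produce apparent harm or hide benefit.

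The direction follows from the design; the size does not. It ranges from negligible (risk ratio about 1.03 at 2% yield and 5% background) to decisive (1.30-1.34 at 20% yield), and it is smaller with 10% background. These figures assume that all positives are scanned, that the whole yield falls on one outcome, and that there is no true effect. The documents do not support a claim that incidence will rise by any particular amount, or that the trial will show the test causing disease. The change is worth making because it is cheap and affects no participant's care.

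**What to change.** In the summary table (outcome 6), the Summary's secondary outcome 6, section 1.5.2 item 6 and section 7.2:

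1. Keep the intention-to-treat incidence comparison, and label it as including screen-prompted detection.
2. Rest any effectiveness or harm conclusion for CVD, COPD and other cancers on endpoints less sensitive to detection, drawn from the same linkage in both arms: unplanned admission with the condition as main diagnosis, and cause-specific death.
3. Show descriptively how many intervention-arm diagnoses followed a study scan, using the incidental-finding record that section 5.1 already requires in the CRF.
4. Split follow-up into the scanning period, including a short lag after the month-24 CT for its work-up, and the time after it.
5. Do not subtract scan-found cases from the intervention arm. Controls have no equivalent deduction, so this would reverse the bias.

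The cost is revised outcome wording and a coding list for the linkage. The detection-insensitive endpoints will have fewer events and wider intervals. They depend less on scanning but not wholly independently of it, since coding of main diagnosis or cause of death can be influenced by disease already known.
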